#### Secondary outcome

2.8.3

##### Scoring scale

2.8.3.1

###### Lysholm scale

2.8.3.1.1

The Lysholm scale assesses knee function in different ligament injuries, with the goal of tracking progress after an intervention and/or evaluating knee deterioration under certain conditions (53). The scale consists of eight components: limping, use of support for walking, instability, pain, locking, swelling, ability to climb stairs, and ability to squat. It is rated on a scale from 0 to 100, where 100-95 is considered excellent, 94-84 is good, 83-65 is fair, and below 65 is poor. Additionally, each component and the total score are analysed separately. This scale has a Cronbach's alpha of 0.737 and an intraclass correlation coefficient of 0.844 (54).

###### Anterior cruciate ligament-quality of life questionnaire

2.8.3.1.2

This scale is a continuous quantitative tool used as a Patient-Reported Outcome Measure to evaluate the effect of ACL injuries on patients' lives. The questionnaire comprised 32 items divided into five domains: symptoms and physical issues (five items), work-related challenges (four items), sports participation/competition (12 items), lifestyle (six items), and social and emotional factors (five items). Each domain receives a score proportional to the number of items and is assessed using a 100-millimeter visual analog scale. Higher scores reflect improved quality of life. This scale was validated in Spanish, showing a Cronbach's alpha of 0.81 and 0.94, and an intraclass correlation coefficient indicating good consistency, ranging from 0.88 to 0.96 (55).

##### Functional assessment

2.8.3.2

Functional Jump Tests are commonly used to evaluate patients after ACL repair, especially to assess the Limb Symmetry Index (LSI) (56, 57). The current literature suggests that the normal LSI is >90% when comparing the ACL-reconstructed limb with the non-operated limb (58). Functional Jump Tests are also cost-effective and simple to assess, as they do not require extensive space or equipment, enabling the evaluation of knee functional capacity and offering a measurable metric that can be tracked over time. Ebert et al. identified eight jump tests—single hop for distance, 6 m timed hop, triple hop for distance, triple crossover hop for distance, single medial hop for distance, single lateral hop for distance, single limb countermovement jump for height, and timed speedy hop test—that were the most effective in highlighting functional limb asymmetries in patients post-ACL injury (59).

##### Psychosocial assessment

2.8.3.3

###### Fear of movement. Tampa scale of kinesiophobia

2.8.3.3.1

The Tampa Scale of Kinesiophobia (TSK) will be used to assess fear of movement or perceived risk of re-injury. This self-reported questionnaire consists of a series of statements, each scored on a 4-point Likert scale ranging from “strongly disagree” to “strongly agree.” Higher scores indicate greater fear of movement or re-injury, whereas lower scores suggest reduced fear levels. It is essential to address kinesiophobia early in the rehabilitation process, as it can negatively impact a patient's adherence to the prescribed rehabilitation program (60). In particular, sports health professionals should be mindful of the influence of kinesiophobia on functional assessments, as it may hinder progress and recovery (61). Research has shown that an increase in kinesiophobia is significantly associated with worse postoperative SF-36 PCS scores, highlighting its negative effect on overall physical functioning in patients after surgery (62). The TSK demonstrates excellent internal consistency, with a Cronbach's alpha of 0.90, and has a proven high test-retest reliability, with an intraclass correlation coefficient (2, 1) of 0.934 (63). Additionally, the severity of kinesiophobia following ACL reconstruction is influenced by factors such as symptom subscales and the Pain Catastrophizing Scale (PCS), further emphasizing the need to consider these factors in the rehabilitation process (64).

###### Pain catastrophizing scale

2.8.3.3.2

The Pain Catastrophizing Scale (PCS) is a self-reported questionnaire designed to evaluate the extent of catastrophizing in response to pain in patients. It consists of 13 items, each rated on a Likert-type scale from 0 to 4, with higher scores reflecting a greater tendency to catastrophize while experiencing pain (65). The PCS is widely used to understand how individuals perceive and react to pain, as catastrophic thinking can significantly influence pain perception and coping strategies. Studies have shown that catastrophizing is a particularly influential factor in the variation of postoperative pain, with adolescents often showing more pronounced effects than adults (66). This suggests that age and developmental factors may play a role in the way catastrophizing influences pain experiences following surgery. The PCS provides a total score ranging from 0 to 52, with higher scores indicating higher levels of catastrophizing. This scale has demonstrated strong psychometric properties, including robust content and construct validity, ensuring that it effectively measures the concept it is intended to assess (67). Additionally, the PCS has been shown to exhibits excellent internal consistency and test-retest reliability, making it a reliable tool for evaluating various musculoskeletal disorders, including those related to injury and surgical intervention (68, 69). Furthermore, the PCS has been found to have significant clinical relevance, as it correlates with both pain intensity and functional outcomes, particularly in long-term recovery. For example, six months after an ACL injury, higher PCS scores were associated with increased pain levels and diminished functional ability (64). These findings highlight the importance of addressing catastrophizing in rehabilitation, as it may contribute to worse recovery. The Spanish version of the PCS has been validated and has good psychometric properties. It has an internal consistency of 0.79, which is considered acceptable, and a test-retest reliability of 0.84, indicating that the scale performs consistently over time in Spanish-speaking populations. These characteristics make the PCS a useful and reliable tool for assessing pain catastrophizing in diverse populations, ensuring that its utility extends across languages and cultures.

##### Cortical excitability

2.8.3.4

Transcranial magnetic stimulation (TMS) is a non-invasive method developed to examine the functionality of human corticospinal pathways (70). Researchers have integrated TMS with EEG and functional imaging techniques to enhance the measurement of cortical excitability. Image guided TMS, with either population-averaged magnetic resonance images (MRIs) or patient-specific MRIs, allows for precise localization of areas of interest. In this study, Brainsight® markers will be positioned on the patient's head using the nasion and zygion as reference points for image-guidance. We will target the hand knob and assess for the motor hotspot—the area of highest motor activity in the injured and non-injured leg's quadriceps and hamstrings muscles using TMS stimulation. Using this hotspot, we will find the motor threshold, or the minimum stimulation required to elicit a response of >50uV in 5 out of 10 TMS pulses. Once the hotspot is identified and the minimum motor threshold established, a 64-channel EEG cap will be placed. EEG recordings will be conducted using a high-density TMS-compatible EEG system (BrainProducts Brain ActiChamp, Gilching, Germany) over the identified hotspot where the minimum motor threshold was obtained with the Brainsight system. The cap allows for the recording of corticospinal and EEG activity (71). For the EEG procedure, the patient will be instructed to contract quadriceps and hamstrings muscles to 30% of their maximum voluntary isometric contraction for 10 s. The patient will receive visual biofeedback through EMG during the contraction, incorporating visual gamification to enhance engagement and performance. The patient will receive visual biofeedback through EMG during the contraction, incorporating visual gamification to enhance engagement and performance. Each contraction will last a maximum of 5 s to avoid fatigue. This process will be repeated three times with intervals between each contraction (72). Latency in milliseconds, amplitude in microvolts, and pulse frequency in hertz will be used to assess cortical excitability and plasticity by recording cortical activity during voluntary contraction (73).

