Leg muscles play a critical role in stabilizing the knee, particularly after an ACL tear, and thus are vital in promoting recovery and preventing re-injury. Research has shown that the hamstrings and hip abductors are essential for minimizing the risk of relapse and addressing functional shortcomings following ACL procedures (19, 20). These muscles protect the knee by counteracting ACL strain as the reconstruction heals. The contribution of muscles to ACL stress and protection varies. Muscles such as the quadriceps and gastrocnemius have shown a higher contribution to ACL stress (21). In contrast, muscles such as the hamstrings, soleus, and gluteus medius have demonstrated a significant ability to counteract ACL strain, aiding in knee stability and injury prevention. Studies using kinematics, EMG, and motor cortex outputs have expanded our understanding of the muscular involvement in ACL injuries. The voluntary activation of the quadriceps in ACL-injured individuals has been studied using measures of cortical excitability. Previous studies have used various metrics, including the active motor threshold and cortical silent period (22), and tested muscles under low-intensity electrical stimulation conditions (23). Following ACL injury, substantial neural adaptations occur within the motor system, significantly affecting voluntary muscle activation and neuromuscular control. Evidence suggests that the cortical representation of leg muscles in the primary motor cortex undergoes reorganisation after ACL, leading to altered patterns of cortical excitability and impaired motor output (24, 25). These neuroplastic changes are particularly evident in the corticomotor pathways associated with the quadriceps, where reduced force-generating capacity is linked to modifications in both intracortical and corticospinal excitabilities (26). Such adaptations are believed to be fundamental for the restoration of motor function, with bidirectional plasticity playing a critical role in the reestablishment of musculoskeletal performance after surgery (27, 28).

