Furthermore, the tDCS device from Ionclinics will be used in the study. The device will be applied during the early stage of rehabilitation, specifically during activation, as the exercises required will be less demanding, less intricate, and more appropriate for this intervention. The treatment plan includes 16 sessions over an 8-week period, with two sessions each week. Each session will administer a continuous current of 2 mA for 20 min. The setup comprises two electrodes (a red anode and a black cathode) and two sponge pads with conductive gel, all incorporated into a helmet tailored to the patient. Electrode placement will adhere to the international 10–20 system for tDCS (46). The primary motor cortex (M1) will be the focus of stimulation, with the anode placed at either C3 or C4, corresponding to the hemisphere contralateral to the injured leg, to target the affected motor area. The cathode will be positioned at the opposite supraorbital area, either Fp1 or Fp2. This placement ensures that stimulation is applied to the motor cortex controlling the injured limb, which is critical for modulating cortical excitability and enhancing the neuromuscular control. The tDCS stimulation will be applied prior to this early rehabilitation phase to ensure proper monitoring and to maximize the safety and efficacy of the intervention*.* The tDCS stimulation will be applied prior to this early rehabilitation phase. Specifically, during the Post-Surgery Recovery Phases 1.1 and 1.2, as well as the Strength and Motor Control Phase 2.1.

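### The TMS procedure names the hand knob as its target although the hotspot is defined by quadriceps and hamstrings response, so leg motor thresholds risk depending on where the coil was placed

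*Protocol article*

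**What the plan says.** Section 2.8.3.4 (Cortical excitability) of the protocol article sets out the TMS procedure in a few linked steps.

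- The target: "We will target the hand knob and assess for the motor hotspot".
- The hotspot, defined in the same sentence: "the area of highest motor activity in the injured and non-injured leg's quadriceps and hamstrings muscles using TMS stimulation".
- The threshold: "Using this hotspot, we will find the motor threshold", with a response above 50 µV in 5 of 10 pulses as the criterion.
- The EEG: "a 64-channel EEG cap will be placed", with recording "over the identified hotspot where the minimum motor threshold was obtained with the Brainsight system".

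The Introduction gives the reason for measuring cortical excitability. It says that "the cortical representation of leg muscles in the primary motor cortex undergoes reorganisation after ACL", and it builds the case for stimulation on changes in the pathways to the quadriceps.

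Table 1 marks the combined EEG and TMS assessment at t1, t3, t5 and tx. Cortical excitability is listed under the secondary outcomes. The primary outcome, in section 2.8.2, is surface EMG of four muscles on each leg.

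**The concern.** The hand knob is a landmark for the hand area of motor cortex. Every muscle of interest here is in the thigh. The sentence therefore gives the operator an anatomical target for one body part and a functional definition for another, and it does not say which governs if they disagree.

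The threshold is the quantity at risk. A motor threshold is interpretable as excitability only if the coil sits over the representation of the muscle being recorded. If it sits elsewhere, a response can still appear when the stimulator output is turned up far enough to reach the leg area by spread of current. The threshold is then raised by distance as well as by low excitability. If the accepted site also differs between operators or visits, a change in threshold over time mixes a change in excitability with a change in coil position.

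The trial's primary hypothesis in the Introduction works through a reduction of excessive excitability in the motor area. Section 2.8.3.4 is the only outcome that measures cortical excitability directly. If its thresholds are noisy or missing because of targeting, a null mechanistic result could not be told apart from a targeting problem, and this could not be repaired after the data are collected.

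**Working it through.** No arithmetic applies. The point depends on no sample size, power, alpha or effect size, and the plan states no figure to reproduce. The check is to set the relevant texts side by side.

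1. **Is any hand muscle measured?** Section 2.8.2.1 lists eight EMG channels: vastus medialis, rectus femoris, vastus lateralis and biceps femoris on the right and on the left. The contraction task during EEG in section 2.8.3.4 uses quadriceps and hamstrings. Hand dominance appears in section 2.8.1 only as a baseline descriptor. So no measurement in the article calls for a hand-area target.

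2. **Does the rationale point to the hand area?** No. The Introduction speaks of the leg representation in primary motor cortex and of the quadriceps pathways.

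3. **Which text governs the final site?** Target and definition stand in one sentence. The definition leads to wherever thigh responses are largest. The target leads to the hand knob. The article does not rank them or call the hand knob a starting point. The sentence also speaks of one hotspot for two muscle groups and both legs, so it does not say which muscle's response decides the site.

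4. **Would the threshold criterion catch a poorly placed coil?** No. The criterion is a response above 50 µV in 5 of 10 pulses. It can be met at a site away from the leg area if intensity is high enough. It tests whether a response was obtained, not whether the site is the best one for that muscle.

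5. **What depends on the site?** The motor threshold depends on it directly. The EEG is described as recorded over the hotspot, but it uses a 64-channel cap, so it depends much less on a single point.

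6. **How far does this reach?** It reaches the TMS assessments at the four columns marked in Table 1, within one secondary outcome. The surface EMG in section 2.8.2 does not use the hotspot at all.

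Steps 1 to 3 show that the named target is an instruction that does not fit the outcome, and not merely a detail left out. Steps 4 to 6 show that the consequence is a risk to the thresholds and is limited in scope.

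**The case against.** The strongest reply is that the definition in the sentence does the work. The hotspot is where the leg muscles respond most, and the threshold is taken there. On that reading the hand knob is a convenient landmark on the image from which to begin, and a poor starting point costs search time without corrupting the final threshold. This reading is fair, and it rules out some stronger conclusions that a reader might draw:

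- **That the thresholds do come from the wrong part of motor cortex.** The document does not support this. It takes them from a hotspot defined by leg response, and it nowhere confines the search to the hand knob.
- **That the EEG is recorded at the wrong site.** A 64-channel cap is not limited to one point, and the hotspot it refers to is again the leg-defined one.
- **That the text contradicts the tDCS placement.** Section 2.7.1 asserts that "This placement ensures that stimulation is applied to the motor cortex controlling the injured limb". Section 2.8.3.4 gives no hotspot coordinates, so there is nothing in the document for the placement to conflict with, and the point here does not extend to it.
- **That the treatment comparison is biased.** The same procedure applies in both arms and the evaluators are to be blinded. The expected harm is added noise and missing values, not a systematic difference between groups.

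It can also be said that a search grid and stopping rule belong in a laboratory manual, and that a journal article need not give them. That is right, and their absence is not the complaint. The complaint is that the article does name a target, and that the one it names does not match the muscles. The benign reading has to be supplied by the reader, because the text says target and never mentions the leg area as the place to search.

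**Conclusion.** The point holds as a mismatch between the stated TMS target and the stated hotspot definition. It creates an avoidable risk that motor thresholds reflect coil position as well as leg corticospinal excitability. It is worth correcting because this is the only outcome that measures cortical excitability, but it does not threaten the primary analysis.

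The size cannot be given as a number. The document supplies no distance, no expected threshold and no rate of failed hotspot searches, so neither the proportion of affected thresholds nor the degree of inflation can be derived. The upper bound on scope is the TMS assessments in the planned 54 participants. The lower bound is no effect, if operators already treat the hand knob as a reference only.

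The conclusion rests on one assumption that the article does not state, namely that the hand and leg are represented at different places in primary motor cortex. This is basic anatomy, and it agrees with the Introduction's reference to a leg representation. The conclusion needs no particular separation between the two.

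**What to change.** In section 2.8.3.4, replace the instruction to target the hand knob with a search that starts at the leg representation of M1 contralateral to the tested leg. If the hand knob is meant only as an anatomical reference on the image, say so instead. In either case:

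- name the thigh muscle whose response decides the hotspot;
- continue the search until the largest response in that muscle is found;
- store the navigation coordinates and reuse them at later visits, so that a change in threshold is measured from the same site.

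This is a change of a sentence or two. The neuronavigation system is already part of the procedure, so no equipment or visit is added. The cost is a slightly longer hotspot search at the first visit. The change has to be in place before the first TMS assessment to which it is to apply, because a threshold taken at a different site cannot be corrected afterwards.

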### Program feasibility and safety: attendance and compliance with protocol

2.9

Several factors influence the adherence of patients with ACL injuries to their exercise regimens. Improving a patient's ability to complete a rehabilitation program, especially home exercises, can be facilitated by considering social and environmental factors that enhance adherence and compliance (74). Furthermore, following the recommended guidelines for return-to-sport clearance after ACL reconstruction is essential for effective rehabilitation (75). Key factors that impact attendance at physiotherapy appointments and participation in sessions include therapist support, rehabilitation setting, and exercise progression (76). For this study, protocol adherence will be measured by calculating the percentage of patients who complete the assessments following established methods from previous research (77). In the initial stages, individualized training will be provided to ensure treatment plan compliance and minimize the risk of adverse effects.

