### Procedure

2.4

After group assignment, all participants will be assessed at four scheduled time points after surgery: one month (post-surgical30), two months (post-surgical60), three months (post-surgical90), and six months (post-surgical180). Scoring scales and psychosocial assessments will be evaluated at each visit (Figure 1). All assessments will be conducted bilaterally to allow within-subject comparisons.

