### Sample size

2.6

The required sample size was determined using GPower® software (Franz Faul, Universität Kiel, Kiel, Germany), version 3.1.9.2. A preliminary sample of 46 subjects, divided into two groups of 23 participants each, was established for the intervention design. The primary variable (EMG output) was used for statistical analysis through repeated measures ANOVA. Cohen's effect size was set at 0.357 based on a previous study examining using surface EMG recordings as their primary outcome (41). The calculation incorporated a statistical power of 0.95, an alpha level of 0.05, and two intervention groups. To account for potential dropouts during treatment follow-up (estimated at 15%), an additional 3 participants were added to each group. This resulted in a total of 54 participants, with 27 per group. The chosen effect size, exceeding 0.357, is classified as “moderate” (42). If a greater percent of participants does not follow their planned treatment protocol (dropouts, non-adherence to treatment, or missing results), an “intention-to-treat” analysis will be conducted.

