#### NIBS_RHB_

2.7.1

A specialized rehabilitation protocol for postsurgical ACL recovery will be implemented. This protocol, grounded in the latest clinical guidelines (43–45), will be structured into four distinct phases: i) post-surgical recovery (weeks 0–5); ii) strength and neuromuscular control (weeks 6–12); iii) running, agility, and landings (weeks 13–24); and iv) return to sport activity (after week 24). The program will encompass 72 sessions scheduled three times a week over a 24-week period. Strength training will be the primary focus of all phases. To ensure optimal patient progress, regular assessments will be conducted with advancement to subsequent recovery phases based on the specific criteria. A schematic representation of the exercise protocol will be employed during rehabilitation (Table 2).

**Table 2 T2:** Phased rehabilitation protocol following ACL reconstruction: objectives, progression criteria, and recommended exercises.

Phase		Weeks	Objectives	Progression criteria	Recommended exercises
Post-surgery recovery	PHASE 1.1	0–2	• Achieve fully extend the knee • Reduce inflammation • Activate the quadriceps • Full extension (0°) • Active quadriceps contraction	• Full extension (0°) • Active quadriceps contraction • Quadriceps Lag Test	• Straight leg raise (SLR): flexion, extension, abduction and adduction • Peripheral joint mobilization • Isometric quadriceps at 90°–60° • Gait training • Inflammation management: cryotherapy + compression
	PHASE 1.2	3–5		• Extension 0° • Contralateral flexion −10° • Absence of inflammation (stroke test)	Strength: • Squat (0°–60°) • Hamstring Curl • Step Up → Step Up + running technique • Lumbo-pelvic strengthening: Clamshell, Side-Lying Leg Raise Bilateral/Unilateral, Hip Hike Balance: • Progression from bilateral to single leg stance • Stationary cycling >100°
Strength and motor control	PHASE 2.1	6–8	• Restore knee strength • Restore muscle strength • Execute Single Leg Stance with proper technique	• Absence of edema • Absence of pain/edema post-exercise • Full Range of Motion (ROM) • Normal gait pattern	• Leg press, Hamstring curl, Hip abduction and adduction, Knee extension (90°–45°), Air squat with band, Deadlift • Single leg squat (SLS) progression • Progression of unilateral balance exercises to include perturbations

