##### Analysis of the outcome measures

2.10.2.2

A per-protocol analysis will be performed in accordance with the CONSORT guidelines for reporting randomized controlled trials. The Kolmogorov–Smirnov test will be utilized to verify the normality assumption, and the Levene test will be used to evaluate the homogeneity of variances. To examine the effects of tDCS combined with exercise-based rehabilitation on patients undergoing ACL reconstruction, repeated measures ANOVA will be applied, with experimental groups as factors and Bonferroni corrections for *post hoc* analysis. Comparisons within and between groups for both primary and secondary outcomes will assess time, group, and interaction effects. Results will be expressed as mean differences (MD) with 95% confidence intervals (CI95%). The effect size (ES) will be calculated using Cohen's d coefficient. All statistical analyses will be conducted using SPSS 24 software (IBM Inc., Chicago, Illinois, USA). If there are participant dropouts or if the statistical power is below 80%, an intention-to-treat analysis will be implemented (78).

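### The only stated adherence measure counts patients who complete the assessments, so it reports retention and cannot show whether the 16 stimulation and 72 rehabilitation sessions were received

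*Protocol article*

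**What the plan says.** Section 2.9 of the protocol article is about attendance and compliance. After discussing what influences attendance at physiotherapy and participation in sessions, it gives one operational rule: "protocol adherence will be measured by calculating the percentage of patients who complete the assessments". It refers to earlier research for the method.

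The treatment is described in section 2.7.1. For rehabilitation, "The program will encompass 72 sessions scheduled three times a week over a 24-week period". For stimulation, "The treatment plan includes 16 sessions over an 8-week period, with two sessions each week". Section 2.7.2 changes the current for the sham arm and gives no different number of sessions, so I take 16 to apply to both arms.

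Assessments are a separate schedule. Section 2.4 says that "all participants will be assessed at four scheduled time points after surgery", at one, two, three and six months.

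Two places in the plan depend on knowing who followed treatment. Section 2.10.2.2 states: "A per-protocol analysis will be performed". Section 2.6 provides for intention-to-treat in these circumstances: "If a greater percent of participants does not follow their planned treatment protocol (dropouts, non-adherence to treatment, or missing results". Section 2.10.2.2 also has its own condition for intention-to-treat, namely dropouts or power below 80%, and does not mention adherence there.

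**The concern.** A trial of an add-on treatment given in repeated sessions needs to know how much of it each patient received. The article sets a rule for adherence, and the rule counts something else. This is more than a detail left to a fuller document: the measure is stated, and an analysis plan that followed it would report retention under the name of adherence.

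Two things are at stake. First, a per-protocol analysis needs a patient-level account of treatment received, and this figure does not supply one. Second, if stimulation was under-delivered, or attendance differed between the arms, the adherence figure need not show it. A null result would then be hard to read, because ineffective stimulation could not be told from stimulation that was not given.

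**Working it through.** The point concerns a definition, so the check is mainly a comparison of sections. The article states no adherence rate to reproduce.

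**1. Treatment to be adhered to (section 2.7.1).**
- Rehabilitation: 3 per week × 24 weeks = 72 sessions, which agrees with the stated 72.
- Stimulation: 2 per week × 8 weeks = 16 sessions, which agrees with the stated 16.

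I do not add the two counts. Stimulation falls in the early rehabilitation phases, and the article does not say whether it takes place on separate attendances.

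**2. What the stated measure counts (sections 2.9 and 2.4).** The numerator is patients who complete the assessments. If these are the scheduled follow-up visits, there are four per patient. No session enters the calculation.

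**3. Where the two diverge.**

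| Patient | Assessments | Stimulation sessions | Stated measure | Treatment received |
|---|---|---|---|---|
| A | 4 of 4 | 0 of 16 | complete | none of the stimulation |
| B | 3 of 4 | 16 of 16 | may count as incomplete | all of the stimulation |
| C (drops out early) | incomplete | incomplete | incomplete | partial |

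Patients A and B are extremes chosen to show the logic. Patient C shows that the measure carries some information: people who leave miss both visits and sessions. It is a poor proxy for treatment received, but it is not empty.

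**4. Level of the measure.** It is a percentage of patients, so it describes the cohort. As worded it gives no individual amount of treatment received. A session-based measure would move in steps of 1/16 = 6.25% for stimulation and 1/72 = 1.4% for rehabilitation, for each patient.

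**5. Against the three items in section 2.6.**
- Dropouts: reflected in assessment completion.
- Missing results: reflected in assessment completion.
- Non-adherence to treatment by someone who stays in the trial: not reflected.

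The article treats the third item as a category of its own, and its one adherence measure cannot detect it.

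**6. Links to the analysis.** Section 2.10.2.2 gives no membership rule for the per-protocol set and does not refer to section 2.9. Neither condition for intention-to-treat is said to use the section 2.9 percentage.

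**The case against.** The strongest reply is that nothing in the article derives the per-protocol set from this percentage, and that a cohort-level figure could not classify individuals anyway. What is left would be an undefined per-protocol set, which an article may leave to the full protocol or analysis plan. The first part stands. A reader might infer that the per-protocol set will include untreated patients and exclude fully treated ones; the documents do not support that. But the finding does not rest on the missing membership rule. It rests on the adherence rule that is stated.

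A reader might also infer that treatment non-adherence could never bring in the intention-to-treat analysis. That is not supported either. Section 2.6 does not say how its non-adherence item is to be judged. Section 2.10.2.2 has a condition that does not use adherence: with 15% dropout expected in section 2.6, intention-to-treat may well apply however adherence is measured. This limits the consequence but does not mend the measure.

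Three smaller objections have some weight. Section 2.7.1 plans regular progress assessments with criteria for moving to the next phase, so gross absence from rehabilitation would probably be noticed by the clinical team. That is not a recorded measure, and it says little about stimulation sessions. The method is referred to a cited source that I cannot see, but the wording in the article is explicit. Lastly, session attendance may be logged in practice. The article does not say so, and if it is, the correction is easier still.

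**Conclusion.** The point holds in a limited form. The stated rule measures retention and calls it adherence. It cannot by itself reveal treatment non-adherence among patients who remain in follow-up, although section 2.6 names that category, and it offers no usable basis for the per-protocol analysis in section 2.10.2.2.

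No numerical size can be given. The article contains neither attendance figures nor a relation between sessions received and effect, so any diluted effect size would only restate an assumption. Poor attendance would also dilute the effect in the randomised sample whichever adherence figure was reported. What can be said is that the stated figure could read 100% at any level of session attendance.

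This rests on reading the assessments in section 2.9 as outcome or progress assessments, not treatment sessions, and on the sham arm having the same 16 sessions. It is a correction that should be made before analysis. It does not undermine the design.

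**What to change.** In section 2.9, define adherence for each patient by two counts: real or sham stimulation sessions received out of 16, and rehabilitation sessions attended out of 72. Report both by arm. Keep the percentage completing the assessments, but label it retention and report it separately.

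In section 2.10.2.2, base per-protocol membership on the two counts, with a cut-off that the trial team chooses and fixes before unblinding. In section 2.6, refer the non-adherence item to the same counts.

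The text changes are short. The practical cost is a per-patient record of sessions attended, which the article does not mention. Stimulation is given with a device in scheduled sessions, so delivery can be noted at the time. The rehabilitation count needs the same entry at each attendance.
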